### Sample size calculation

For sample size calculation, the difference in handgrip strength from the first assessment point (AP1) to the second assessment point (AP2), which take place 10–12 weeks after AP1 (see Figure 
1), is considered as a marker of muscle strength. We examine its relationship with diet
[24,33] and physical activity
[34] in a community-dwelling cohort. Given a clinically relevant difference of 2 kg in handgrip strength (intervention group improves by 2 kg more than the control group in handgrip strength), a standard deviation of 3 kg of the differences, a two-sided significance level of 0.05, a sample size of n = 36 per group is needed to reach 80% statistical power. Since imputation for drop-outs may have some inestimable effect on the assumed standard deviation of the differences, the sample size is increased to n = 40 per group. Expected value μ1 (intervention) = 16 kg, μ2 (control) = 14 kg (based on the results of the pre-study
[42,44]). The primary endpoint is analyzed according to the intention-to-treat principle (ITT).

### Randomization

Persons are randomly assigned to the intervention or control group, stratified by handgrip strength with the help of the “Randomizer for Clinical Trials 1.8.1″
[45]. Randomization is carried out after the patient has signed the informed consent and has been matched to a lay buddy, dependent on the place of residence.

### Intervention

In the first 10–12 weeks each couple (one buddy and one malnourished frail person) is divided randomly into the intervention and the control group.

### Control group

Participants in the control group are visited twice a week by buddies, but they do not specifically monitor the nutritional status or perform physical training in the first 10–12 weeks. Instead of that, buddies are provided with a portfolio of possible activities, especially cognitive training, which they could perform together with the frail malnourished person. After 10–12 weeks the control group also receives nutritional intervention and the physical training for 3 months.

### Intervention group

Buddies visit malnourished frail older persons twice a week for approximately one hour and they perform nutritional and physical activity interventions.

#### Activities for improving nutritional habit

The aim is to obtain adequate protein, energy and other nutrient intake, preferably by regular foods and beverages. Therefore, buddies discuss the following three main nutritional messages with the malnourished frail persons: fluid intake**,** animal and plant protein intake and energy intake. For this purpose, buddies are equipped with a portfolio in which the topics concerning physical activity and nutrition are explained in a straightforward manner. Moreover, they obtain ideas how to enrich food with protein and receive recipes of dishes which are protein and energy dense.

In order to show the variance of recommended and actual food intake, buddies are equipped with the “Healthy for Life Plate” which is a modification of the Health Eating Plate of the Harvard University
[46]. It consists of a play board and food-cards representing a variety of foods (Figure 
2).

**Figure 2 F2:**
[figure not shown]
Healthy for life plate.

One food-card shows one portion size. Buddies and malnourished frail persons should set these food-cards, which they have eaten the day before, on the play board. The “Healthy for Life Plate” assesses the quantity and the composition of daily food rations. Therefore, with the game, dietary behavior can be examined and consequently optimize dietary habits. For convincing malnourished frail persons to change their nutritional habits, buddies additionally use motivational interviewing techniques
[47]. Due to this fact every nutritional message includes a section for individual goal setting and tools to reinforce the self-efficacy. As it is done in the motivational-volitions-concept
[48], every message also includes a part which should reveal problems of implementing the goal in everyday life, in order to find solutions for them.

#### Physical intervention

Twice a week strength training is performed by malnourished frail persons together with the buddies. The training comprises a warm-up (about five minutes, mobilization exercises) followed by six strength exercises, which are performed in circuit form with two sets. The exercises are conducted with 15 repetitions until muscular exhaustion. The performed exercises can be retained from Table 
2. This circle lasts about 30 minutes. Moreover, buddies talk about the relevance of health enhancing physical activity in connection with frailty. Further on, they discuss possible arising problems, talk about their baseline activity and set individual goals concerning physical activity. For personal motivation buddies and frail people get a pedometer. Additionally, buddies advise the malnourished frail elderly to practice the same strength exercises once a week on their own.

**Table 2 T2:** Description of the six strength exercises

**Basic exercise**	**Alternative exercise**	**Muscle group**
▪Mini squat in front of a chair (with the help of a table)	▪Lunges	▪Femoral muscles
▪Chest Press against elastic resistance - sitting on a chair	▪Chest Press against the wall	▪Pectoral muscles
▪“beetles” - sitting on the chair		▪Abdominal muscles
▪Hip extension - standing position	▪Hip extension - standing position against elastic resistance	▪Ischiocrural muscles
▪Reverse Butterfly against elastic resistance - sitting on a chair		▪Upper back muscles
▪Shoulder press against elastic resistance - sitting on a chair		▪Muscles of the arms, and shoulders

#### Materials for the intervention group

Participants of the intervention group receive a bag which contains the following materials: a guidebook including messages regarding health promoting nutrition, detailed information on health enhancing physical activity and all strength exercises shown as pictures, a recipe book with dishes high in energy and protein, a dynaband for exercising, a demonstration DVD for guidance and motivation and a pedometer for counting food steps. Additionally, in the box there is the “Healthy for Life Plate”. Buddies are also equipped with a documentation book, where they should record the content of each home visit.

### Training of the buddies

The project team, consisting of three sport scientists, two nutritional scientists and one medical doctor, trains the buddies of the intervention and the control group 4 times for 3 hours each session. This training starts 4 weeks before the first appointment with the malnourished frail persons will take place (Figure 
3).

**Figure 3 F3:**
[figure not shown]
**Training of buddies.** AP: Assessment point. M1: Meeting to discuss open questions from the buddies concerning the interventions. M2: corrective training for the control group.

The sessions comprise lessons concerning aging, frailty, malnutrition, main nutritional messages, which are described in the section intervention group, and the importance of health enhancing physical activity, focusing on strength training and baseline activity. Moreover, buddies learn about the key issues of motivational interviewing skills. Buddies additionally get to know the interventions conducted with the control group. Training is designed interactively and enables buddies how to enrich dishes with regards to the energy and protein intake. They practice the motivational interviewing skills and can taste food. Furthermore, the project team exercises together with buddies in order to show them the right performance and intensity of each strength exercise and they discuss their pedometer data with them.

Two to three weeks after the beginning of the intervention, the buddies and the project team meet again to discuss arising questions and exchange experiences.

Buddies in the control group get another training to refresh their knowledge before they start with the nutritional and physical activity intervention after 10–12 weeks of the initial period.

### Measurements

All involved persons, malnourished frail elderly people and buddies, are evaluated at four points in time: before the intervention (AP1), after 10–12 weeks (AP2), after 6 months (AP3), and after 12 months (AP4). Malnourished frail persons are measured at their home and all buddies are surveyed after the last training of the buddies, respectively. Not all measurements take place at each time point. Table 
3 gives a summary of the conducted measurements at several times (AP1, AP2, AP3, AP4) in malnourished frail elderly persons (F) and buddies (B).

**Table 3 T3:** Measurements at several timepoints in malnourished frail elderly persons (F) and buddies (B)

	**Selection**	**AP1 (baseline)**		**AP2 (after 12 weeks)**		**AP3 (after 6 months)**		**AP4* (after 12 months)**	
	**F**	**F**	**B**	**F**	**B**	**F**	**B**	**F**	**B**
Long-term medication	X								
Comorbidities	X								
WHOQOL		X	X	X	X	X	X		
WHOQOL-OLD		X		X		X			
F-SozU		X	X	X	X	X	X		
Frequency of hospitalization		X		X		X			
Frequency of falls		X		X		X			
FES-I		X		X		X			
MNA-SF	X								
MNA-LF		X		X		X		X	
SHARE-FI	X			X		X		X	
MMSE	X			X		X		X	
BIA		X	X	X	X	X	X	X	X
Anthropometry		X	X	X	X	X	X	X	X
MEDIAS		X	X	X	X	X	X		
Food frequency questionnaire (Proteins)		X	X	X	X	X	X		
Supplements		X	X	X	X	X	X		
Protocol & picture of the refrigerator content		X		X		X			
MASS		X	X	X	X	X	X		
Concept 2 Dyno			X		X		X		
Pedometer			X	X	X	X	X		
Modified PASE		X	X	X	X	X	X		
Modified FEG			X		X		X		
SPPB		X		X		X			
Laboratory parameters		X	X	X	X	X	X		
Personal information		X	X						
Drop-out				X	X	X	X	X	X
Adherence				X	X	X	X	X	X
Expectations/appraisal of the intervention		X	X	X	X	X	X	X	X

WHOQOL = World Health Organization Quality of Life; F-SozU = Fragebogen zur sozialen Unterstützung; FES-I = Falls Efficacy Scale International; MNA-SF = Mini nutritional assessment Short-Form; MNA-LF = Mini nutritional assessment Long-Form; SHARE-FI = Frailty Instrument for Primary Care of the Survey of Health, Ageing and Retirement in Europe; MMSE = Mini-Mental State Examination; BIA = Bioelectrical Impedance Analysis; MEDIAS = Mediterranean Diet Adherence Screener; MASS = Measurement of age and sex related reference values of muscle strength; PASE = Physical Activity Scale for the Elderly; FEG = Fragebogen zur Erfassung des Gesundheitsverhaltens; SPPB = Short Physical Performance Battery.

*AP4 is voluntary.

The following measurements are performed:

Measurements of health status:

• *Quality of life* assessed by the World Health Organization Quality of Life WHOQOL-BREF
[49] and by 3 dimensions of the WHOQOL-OLD (“sensory functions”, “autonomy”, “activities in the past, present and future”)
[50]

• *Social support* measured with the short version of the questionnaire F-SozU
[51].

• *Frequency of hospitalization*

• *Frequency of falls*

• *Documentation of fear of falling* assessed by the FES-I (Falls Efficacy Scale-International Version)
[52]

Measurements of frailty, nutritional status, physical activity:

• *Frailty status* assessed by the SHARE-FI (Frailty Instrument for Primary Care of the Survey of Health, Ageing and Retirement in Europe)
[3]. According to the results of the SHARE-FI, persons are categorized in frail, pre-frail, and robust people divided by gender. The handgrip strength, which is the primary endpoint of the study and part of the SHARE-FI, is measured with a hydraulic dynamometer in standardized procedure
[53]. For each side three attempts are made, and the highest one is used for calculation.

• *Nutritional status* assessed by the long form of the MNA (Mini Nutritional Assessment)
[54]. In our study calf circumference is used which is measured with a tape at the sitting patient on the left and the right lower leg at the strongest circumference
[55]. Different to the protocol, persons put their feet on the floor while measuring.

• *Cognitive function* assessed by the German version
[56] of the MMSE (Mini Mental State Examination)
[57].

• *Body mass index (BMI; kg/m*^
*2*
^*)* while body height is assessed by a yardstick and body weight by a calibrated scale.

• *Body composition* assessed by the BIA (Bioelectrical Impedance Analysis) in standardized procedure
[58]. Moreover, waist circumference is measured at a vertical level 2.5 cm above the umbilicus while expiration
[59].

• *Quality of the diet* assessed by the Mediterranean Diet Adherence Screener (MEDIAS)
[60], a food frequency questionnaire assessing the protein intake and questions concerning supplements
[61].

• *Qualitative and quantitative contents of refrigerators* assessed by a predefined protocol and picture of refrigerator
[62].

• *Muscle strength* assessed by the MASS (Measurement of age and sex related reference values of muscle strength) and the Concept 2 Dyno. The MASS is a new diagnosis system which was developed by the Technical University of Vienna. It evaluates health related concentric dynamic muscle strength. The measurement is velocity-independent and hence, is appropriate for the target group. Three exercises (bench press, bench pull, and leg press) will be conducted in standardized procedure. For all tested muscle groups the following parameters are recorded: maximum resistance with low velocity and 2–3 fix adjusted sub-maximum loads. Moreover, the Concept 2 Dyno is used for assessing the muscle strength. The same exercises as before will be conducted in standardized procedure
[63].

• *Daily physical activity* assessed by an activity sensor (pedometer), the modified PASE (Physical Activity Scale for the elderly)
[64] and the modified questionnaire on health-related behavior FEG (Fragebogen zur Erfassung des Gesundheitsverhaltens)
[65]. The pedometer-data will be analyzed as follows: Data from the week before AP2, AP3 and AP4 will be included in the analysis. Data of those who have used the pedometer less than four days are excluded. Days, on which the pedometer was used less than eight hours, are considered as invalid. The number of steps below 90 steps per minute, the number of steps above 90 steps per minutes and the walk time is analyzed.

• *Balance and mobility components* assessed by the SPPB (Short Physical Performance Battery)
[66].

• *Laboratory parameters* for malnutrition or frailty (albumin, total cholesterol, transferrin, triglyceride, 25-hydroxy-vitamin D, folic acid, CRP, IL-6, TNF-alpha and leucocytes)

Other measurements

• *Personal data* e.g. age, gender, family status, education level, income, occupation

• *Measures of drop-out (DO)*[67]*:* the drop-out rate between the first and second visit and until the final visit should be analyzed. For each case of discontinued participation (Ri), the following reasons are discriminated: medical reason (R1) and person’s own decision (R2), whereas an “A” stands for all participants who passed the baseline assessment.

• Drop-outs between the first and second visit:

⋅DO_R_ = DO_1_ + DO_2_ – all participants who drop out between the first and second visit

⋅DO_R1_ = DO_1_/A – percentage of participants who discontinue by medical reasons.

⋅DO_R2_ = DO_2_/A – percentage of participants who discontinue on their own decision. Members of this group are asked for a personal reason (voluntary and open question), and also be asked to participate in the final visit.

• Drop-outs until the final visit

⋅|DOR| – total number of participants who drop out until the final visit

⋅IDORI = IDO1I + IDO2I – all participants who drop out until the final visit

⋅IDOR1I = IDO1I/A – percentage of participants who discontinue by medical reasons.

⋅IDOR2I = IDO2I/A – percentage of participants who discontinue on their own decision.

• *Measures of adherence* are calculated as:

⋅Number of home visits

⋅Number of activity units, which have been done without buddies respectively without malnourished frail people

⋅Number of discussed nutritional messages

• *Expectations/Appraisal of the interventions by participant (malnourished frail persons and buddies)*[67]*:* following questions are asked, “Would you once again participate in the trial? Why/why not?”. Participants, who completed the intervention, are asked to rate the content of the nutritional and physical activity interventions, the length of the program, and the frequency of home visits. Moreover, they should score (on a scale from one to five) the utility of the materials, which they received e.g. guidebook, dynabands, pedometers, training DVD or VHS, the “Healthy for Life Game” and questionnaires. Buddies should also rate the training sessions and the documentation book. Finally, concrete proposals for program improvements are asked, “Do you have any ideas or proposals for program improvements?”.

• *Documentation of any undesirable event during the intervention:* Any symptom or any disease of a participant, which occurs during the intervention, is called an undesirable event
[67]. This definition is valid, whether this event is caused by the intervention or not. In case of an undesirable event, the participant promptly has to suspend nutritional and exercise units and they have to visit a physician. The event has to be documented by a standardized report protocol, including the following judgments: medical/non-medical, caused/not caused by exercises and people may/may not continue nutritional and exercise units.

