**Methods/design:**

In this randomized controlled trial, 80 malnourished frail community-dwelling patients (≥ 65 years) hospitalized at wards for internal medicine are recruited. Additionally, 80 lay volunteers (≥ 50 years), named buddies are recruited and subsequently trained regarding health enhancing physical activity and nutrition in four standardized training sessions. These buddies visit the malnourished frail persons at home twice a week for about one hour during an initial period of 10–12 weeks. While participants allocated to the intervention group (n = 40) receive intervention to improve their fluid intake, protein and energy intake, perform strength training and try to increase their baseline activities, the control group (n = 40) only gets home visits without any intervention. After 10–12 weeks, both, the intervention and the control group, receive the nutritional intervention and the physical training. Health, nutritional and frailty status, physical fitness, body composition and chronic inflammation of buddies and frail persons are recorded before the intervention, after 10–12 weeks, 6 and 12 months.

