#### Buddies

The buddies are recruited in cooperation with the “Wiener Hilfswerk” in four waves within one year. The “Wiener Hilfswerk” is one of the largest organizations in Austria, which already offers care-giving services for elderly persons carried out by volunteers. The inclusion criteria for buddies are:

• 50 years or older

• Readiness to participate in the study either in the intervention or control group

• Commitment to keep to the protocol for at least 6 months

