### Statistical analysis

Data exploration using descriptive statistical analysis and inferential statistics is performed. The sample data is carried out by frequencies or percentages, means and standard deviation, and graphics. 95% confidence intervals (CI) are calculated for the differences in percentages and medians. T-test and chi-square test is used to compare groups at baseline. Moreover, Pearson’s- and Spearman’s correlation coefficients is used. In order to test the normal distribution, histograms and box plots will be applied. If normal distributions are not met, non-parametric tests such as Wilcoxon, Mann–Whitney-U-Test and Kendall’s tau and Spearman’s correlation coefficients are chosen. Analysis of covariance (ANCOVA), comparing parameters after the intervention (AP2) and after the follow-ups (AP3, AP4) between intervention and control group, adjusting for the baseline value as covariate is performed. The IBM® SPSS® Statistics for Windows, Version 20 software (IBM Corp., Armonk, NY, U.S.) is used for all statistical analyses. All tests are two-sided and a p-value <0.05 is considered statistically significant.

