A crucial point of the study is the compliance of both parties on regularly performing the strength exercises with correct intensity. Hence, all four buddy training sessions focus on this issue. Another crucial point is the ability of buddies to motivate frail malnourished persons to improve their nutritional habits. As the buddies are non-professionals, the nutritional interventions focus on the main “topics”. In detail, these topics contain information and recommendations on nutrition and additionally suggestions on the implementation in everyday life e.g. modified traditional recipes with tips on protein enrichment or portion sizes shown as handful in pictures.

The main objectives of these nutritional and physical activity interventions are the evaluation of the applicability of this program carried out by buddies and especially the sustainability that older people may live independently at home and as long as possible, which offers new methods for the management of frailty.

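### The 12-month assessment (AP4) is stated as covering everyone but footnoted as voluntary, yet it gets the same between-arm ANCOVA as AP2 and AP3

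*Protocol article*

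**What the plan says.** The Measurements section opens with a general rule: "All involved persons, malnourished frail elderly people and buddies, are evaluated at four points in time", namely AP1 to AP4, with AP4 at 12 months. The abstract says that the outcomes of both groups "are recorded before the intervention, after 10–12 weeks, 6 and 12 months". It does not use the word all, but it gives 12 months no different standing.

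The asterisk on the AP4 column of Table 3 leads to the footnote "AP4 is voluntary". AP1, AP2 and AP3 have no such mark. The inclusion criteria for buddies ask for "Commitment to keep to the protocol for at least 6 months", so AP4 falls after that minimum.

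For frail persons, Table 3 schedules MNA-LF, SHARE-FI, MMSE, BIA and anthropometry at AP4. Handgrip strength is measured as part of SHARE-FI.

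The Statistical analysis section plans an ANCOVA with the baseline value as covariate, "comparing parameters after the intervention (AP2) and after the follow-ups (AP3, AP4) between intervention and control group". AP4 is neither separated from the other time points nor labelled differently.

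**The concern.** Any participant may decline any trial visit, but here the plan itself makes one visit optional and then tests the arms at that visit as it does at the others. Those who come to AP4 choose to do so after randomisation and after going through the programme. In a frail, recently hospitalised population, that choice plausibly depends on health and on satisfaction with the programme.

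Two things could follow. Attenders may look better than all those randomised, within each arm. If attendance, or its relation to outcome, differs by arm, the AP4 difference between arms may also be biased. A reader of the ANCOVA sentence would take the AP4 result as a comparison of the randomised groups with the same standing as AP2.

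The Overview has home visits running for 6 months, so AP4 is the one assessment well after the programme. That makes it the natural source for any statement about lasting effects.

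**Working it through.** **1. The passages side by side.** The Measurements text has everyone assessed at AP4. The Table 3 footnote makes AP4, and only AP4, voluntary. The Statistical analysis section names AP4 in the same between-arm test as AP2 and AP3. The article itself states both the voluntary rule and the test, so this is more than a detail left for another document.

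**2. The plan's own figure.** The Sample size calculation section uses a difference of 2 kg, an SD of 3 kg for the AP1 to AP2 change, two-sided 0.05 and 80% power:

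n = 2 × (1.960 + 0.842)² × 3² / 2² ≈ 35.3, rounded up to 36 per group.

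This reproduces the stated 36, which the plan raises to 40. It concerns AP2 and is not in question.

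**3. A sketch of possible selection at AP4.** From the document: SD 3 kg and 40 per arm. Assumed: attendance p in each arm, a normal latent attendance variable with correlation r = 0.2 to 0.5 with handgrip change, no true difference between arms, and no baseline adjustment.

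Shift in the mean among attenders = r × SD × φ(z) / p, where z is the standard normal quantile of p.

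- p = 0.8: φ(z)/p = 0.280/0.8 = 0.350
- p = 0.6: φ(z)/p = 0.386/0.6 = 0.644

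Within an arm at 60% attendance, the shift is 3 × 0.644 × r, or 0.39 kg (r = 0.2) to 0.97 kg (r = 0.5).

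Between arms at 80% v 60%, the difference is 3 × (0.644 − 0.350) × r = 0.882 × r, or 0.18 to 0.44 kg. That is 9% to 22% of the 2 kg relevant difference. The standard error of the difference is 3 × √(1/32 + 1/24) = 0.81 kg, so the bias is about 0.2 to 0.5 standard errors.

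| Attendance by arm | r = 0.2 | r = 0.5 |
|---|---|---|
| 70% v 70% | 0 | 0 |
| 80% v 60% | 0.18 kg | 0.44 kg |
| 70% v 50% | 0.18 kg | 0.45 kg |
| 60% v 40% | 0.19 kg | 0.48 kg |
| 90% v 50% | 0.36 kg | 0.90 kg |

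With positive r, the bias favours the arm with the lower attendance, so it could work for or against the intervention.

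**4. Limits of the sketch.** The 3 kg is the SD of the AP1 to AP2 change, because none is given for AP1 to AP4. The planned ANCOVA adjusts for baseline, which would absorb at least part of any selection acting through the baseline level. The attendance rates and correlations are assumptions.

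**The case against.** The strongest reply is that the general sentence leads the reader to Table 3, where the asterisk discloses that AP4 is voluntary. On that reading the footnote qualifies the text, and there is no real conflict. The ANCOVA sentence also does not say that only attenders are analysed, and handling of missing secondary data is commonly left to an analysis plan that is not shown. Table 3 marks drop-out at AP4, and the Measurements section counts drop-outs with reasons up to the final visit.

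Much of this stands. The mismatch is one of wording, and silence on missing-data methods is no fault in an article. But disclosure in a footnote does not carry over to the Statistical analysis section, which gives the voluntary time point the same standing as the others. The drop-out measures are not broken down by arm.

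Three stronger readings are tempting, and the document supports none of them:

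- **That the AP4 results will be biased.** Bias is possible, not established. It is zero between arms if attendance and selection are equal, and by AP4 both arms have had the programme, so unequal attendance is not self-evident.
- **That a main objective of the trial rests on AP4.** The Discussion speaks of "especially the sustainability that older people may live independently at home and as long as possible", which is general and tied to no 12-month endpoint. The Study objectives section names no 12-month objective.
- **That full attendance would give a treated-versus-untreated comparison at 12 months.** It would not: "After 10–12 weeks the control group also receives nutritional intervention and the physical training for 3 months". AP4 compares early with delayed intervention in any case.

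**Conclusion.** The point holds, and it is minor. The text and its footnote differ on who is assessed at 12 months, and the analysis section treats a voluntary follow-up as equal in standing to AP2 and AP3. The AP4 comparison may be affected by self-selection and should not be presented on the same footing.

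Its size and direction are unknown. At an assumed 80% v 60% attendance it would be about 0.18 to 0.44 kg of handgrip strength, below one standard error. Larger figures need a wider gap, and equal attendance with equal selection gives no between-arm bias. All of this depends on the assumed rates and correlations, the SD borrowed from AP1 to AP2, and the absence of baseline adjustment.

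Only secondary outcomes are touched. The primary endpoint, its intention-to-treat statement and the sample size all concern AP2 and stand as they are.

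**What to change.** 1. In the Measurements section, state in the text that AP1 to AP3 are for everyone and AP4 is voluntary, as the footnote has it.
2. In the Statistical analysis section, separate AP4 from AP2 and AP3 and label it exploratory follow-up of volunteers.
3. Report AP4 attendance by arm, with the AP1 to AP3 values of attenders and non-attenders.
4. If a between-arm AP4 estimate is kept, take it from a mixed model that uses all available assessments of all randomised persons. This reduces selection bias explained by observed data. It does not remove selection that depends on the unobserved AP4 outcome itself.

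Merely declaring AP4 a visit that all are asked to attend, while they may still decline, would change little.

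The cost is a wording change, a little more analysis and a more cautious 12-month conclusion. No extra visits are needed.
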